## Risks and Benefits of the Study:

**The study involved minimal risk.** The two procedures—multisession (a-tDCa) targeting the PFC, combined with exercise (E) and pain education (PEN)—had been previously studied in home settings, with no reports of serious complications or brain damage. tDCS used a low-intensity current, which was safe for fibromyalgia, with the most common side effect being mild scalp tingling, minimized by humidifying the electrodes with saline.

The main benefit for participants was the potential improvement in pain-related symptoms of fibromyalgia. Participants could also join a 3-month follow-up phase, where a-tDCS -E-PEN was offered in an open phase. Although the study took

place at home, patients visited the research center for periodic clinical evaluations and had remote access to the research team for questions and updates. Any clinical complications were treated at the Hospital de Pronto Socorro, Porto Alegre, Brazil, with treatment provided free of charge as needed.

After the study, participants were referred back to their original outpatient clinics with appropriate prescriptions and care instructions

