### f.4. Sample size estimation

The primary outcome of this study, pain-related function, is measured using the 7-item Brief Pain Inventory (BPI) interference scale. This scale serves as a Multidimensional Pain Interference Index (MPII), providing a comprehensive view of how pain affects various dimensions of an individual's life, including emotional well-being, social interactions, and daily activities. Focusing solely on pain severity may fail to reflect the full impact of pain on a person's overall quality of life. The secondary outcome, pain intensity, is evaluated using the 2-item BPI severity scale. Both BPI scales range from 0 to 10, with higher scores representing worse function or intensity. Understanding the Minimal Clinically Important Differences (MCID) changes in pain interference scores is vital for clinicians to determine whether changes are significant enough to indicate meaningful improvements or declines in quality of life, rather than just being statistically significant. According to previous studies in chronic pain populations, an MCID of approximately 0.7 points for both the BPI interference and severity scales has been identified. However, consensus guidelines have established a 1-point difference as the MCID for both scales, while a 30% reduction from baseline is also recognized as a significant indicator of moderate improvement. In examining the effects of E-PNE with a-tDCS and s-tDCS groups at the final time point (moment 5), which occurs three months post-treatment, a more conservative MCID of 0.6 points was used for estimating the sample size. This cautious approach aims to ensure a thorough evaluation of the study's power to assess the treatment effects. The sample size estimation was performed using the PSS *Health tool* 32. [https://hcupa-unidade-bioestatistica.shinyapps.io/PSS\\_Health/](https://hcupa-unidade-bioestatistica.shinyapps.io/PSS_Health/). To detect a minimum difference of 0.6 points between the means of the Multidimensional Pain Interference Index (MPII) for the a-tDCS group and the s-tDCS group at the final time point (moment 5) in a repeated measures analysis, a sample size of 94 participants (47 per group) was calculated. To account for a potential dropout rate of 15%, the sample size was increased to 112 participants. This calculation was based on an

assumed 80% power, a 5% significance level, and relevant parameters for the treatment group.

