### **Primary Outcome**

- i. Pain interference was assessed using a multidimensional pain score from the Brief Pain Inventory (BPI), which evaluates seven daily activities: general activity, walking, work, mood, enjoyment of life, relationships, and sleep. BPI pain interference scores range from 0 to 10, with 0 indicating no interference and 10 indicating complete interference. Overall pain interference was calculated as the mean of the seven items. The assessment was conducted over a 4-week treatment period and at three months of follow-up .

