### **Clinical Measurements: Included assessments of depressive symptoms, central sensitization, sleep quality, analgesic use**

- x. Demographic Data and Medical Comorbidities: Collected via a standardized questionnaire.
- xi. Psychological Assessments: Included the Pittsburgh Sleep Quality Index (PSQI)  and the Central Sensitization Inventory for the Brazilian Population (CSI-BP)  with scores indicating symptom severity. Depressive symptoms were assessed using the Beck Depression Inventory II, and the Pain Catastrophizing Scale (PCS) evaluated catastrophic thinking about pain .

- xii. Analgesic Use: Patients were allowed to take additional medications as needed and were instructed to record their intake in diaries. The total dose taken each week during the treatment period and three-month follow-up were used for analysis.

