### Schedule of assessment.

|                                                                      | Baseline | Week1 | Week2 | Week3 | Week4 | 3-month follow-up |
|----------------------------------------------------------------------|----------|-------|-------|-------|-------|-------------------|
| Sociodemographic and lifestyle questionnaire                         | X        |       |       |       |       |                   |
| 2016 American College of Rheumatology Diagnostic Criteria (ACR-2016) | X        |       |       |       |       |                   |
| Central Sensitization Inventory                                      | X        |       |       |       |       |                   |
| Pain Catastrophizing Scale                                           | X        |       |       |       | X     |                   |
| Beck Depression Inventory (BDI-II)                                   | X        |       |       |       | X     |                   |
| Pittsburgh Sleep Quality Index (PSQI)                                | X        |       |       |       | X     |                   |
| Outcomes                                                             | X        |       |       |       |       |                   |
| Brief Pain Inventory (BPI)                                           | X        | X     | X     | X     | X     | X                 |
| Patient Global Impression of Improvement (PGI-I)                     |          |       |       |       | X     |                   |
| Fibromyalgia Impact Questionnaire (FIQ)                              | X        |       |       |       | X     |                   |
| Conditioned Pain Modulation (CPM-test)                               | X        |       |       |       | X     |                   |
| Side effects of tDCS questionnaire                                   |          |       |       |       | X     |                   |

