### Schedule of activities

|                                            |                   |                                |
|--------------------------------------------|-------------------|--------------------------------|
| Step Identification                        | Beginning         | Term Screening of participants |
| Screening of participants                  | October 9, 2021   | March 3 , 2022                 |
| Double-blind and randomized phase          | April 01, 2022    | April 10, 2022                 |
| Open follow-up phase                       | May 15, 2023      |                                |
| Analysis of data from the randomized phase | July 08, 2024     | December 15 2024               |
| Open phase data analysis                   | February 10, 2024 | July 10, 2024                  |

We assure that the FIBRO-HB-tDCS study was initiated only after receiving approval from the CEP-CONEP (Ethical Review Board) System of the Hospital de Clínicas de Porto Alegre, the university hospital of the Federal University of Rio Grande do Sul (UFRGS), Porto Alegre, Brazil.

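### The trial is sized on the three-month BPI, yet open active tDCS is offered in a three-month follow-up phase with no rule that it waits for that assessment

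*Protocol*

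**What the plan says.** Section f.4 (Sample size estimation) places the design comparison "at the final time point (moment 5), which occurs three months post-treatment". It seeks a 0.6-point difference in the BPI interference index with 80% power at the 5% level, which gives 94 participants, raised to 112 for dropout. The Primary Outcome section includes the same time point: "The assessment was conducted over a 4-week treatment period and at three months of follow-up". The Schedule of assessment has a BPI entry for it under the column "3-month follow-up". The analgesic-use item under Clinical Measurements treats the interval as part of the analysed trial: "The total dose taken each week during the treatment period and three-month follow-up were used for analysis".

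The Risks and Benefits section then says: "Participants could also join a 3-month follow-up phase, where a-tDCS -E-PEN was offered in an open phase". The Schedule of activities has a row named "Open follow-up phase", starting 15 May 2023, and plans a separate analysis of open-phase data.

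Two other statements bear on the question. The structured visit sequence ends at the week-4 visit, when the device is handed back. Section 3 says the device is programmed for a fixed number of sessions at least 16 hours apart.

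**The concern.** The sized endpoint and the open active-treatment phase have the same length and nearly the same name, and no rule puts one before the other. A sham participant who takes open a-tDCS before the three-month BPI is no longer a sham control when that BPI is recorded. She also knows what she is receiving when she rates her own pain interference.

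If sham participants gain more from open treatment than active participants who also join, the difference between arms shrinks towards zero. If active participants who join gain as much or more, the loss may be offset or reversed. In either case the three-month contrast would no longer compare a-tDCS with sham.

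When control participants may receive the active treatment is a rule of conduct. It belongs in the protocol and is not a detail to leave to an analysis plan.

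**Working it through.** **1. Reproducing the stated sample size.** Inputs from section f.4 and its R code: difference 0.6; SD 1 in each arm; first-order autoregressive correlation 0.4 (a-tDCS) and 0.2 (s-tDCS); retention 100, 99, 98, 96 and 94% at moments 1 to 5; 80% power; 5% level. The Statistical Analysis section states two-tailed tests.

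The repeated-measures formula is n per arm = (φa·SD² + φb·SD²)(z0.975 + z0.80)² / difference². Here φ is the last diagonal element of the inverse of the retention-weighted information matrix. The inputs give φa = 1.0597 and φb = 1.0629.

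n = (1.0597 + 1.0629) × (1.960 + 0.842)² / 0.36 = 46.3, so 47 per arm and 94 in total, as stated. For 15% dropout, 47 / 0.85 = 55.3, so 56 per arm and 112 in total, as stated. The sizing is sound for an uncontaminated comparison at moment 5.

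**2. Can the protocol's text or dates put the open phase after moment 5?**

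- *Per-participant rule:* none. The visit sequence stops at week 4, so the interval from week 4 to the three-month BPI is not described.
- *Scheduled data:* the Schedule of assessment has only one column after week 4, the three-month follow-up. An analysis of open-phase data is planned, but no separate open-phase assessment is scheduled.
- *Calendar:* the row reads "Double-blind and randomized phase | April 01, 2022 | April 10, 2022". That is 10 days inclusive, against 28 days for the four-week treatment, so the row cannot be right as printed. The screening row, "Screening of participants | October 9, 2021 | March 3 , 2022", ends before the double-blind row begins and gives no accrual period from which to reconstruct it.
- *As printed:* four weeks plus three months from 10 April 2022 ends about 8 August 2022, well before 15 May 2023, so there is no overlap.
- *If the end date was meant to be 10 April 2023 (assumption):* the open phase starts 35 days later. That is safe if the row includes moment 5. If the row covers treatment only, anyone finishing treatment after 15 February 2023 would have her three-month BPI due after open treatment became available.

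The table cannot decide between these readings.

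**3. Illustration of size.** Let f be the share of the sham arm that takes open a-tDCS before moment 5. Assume each gains the full 0.6 and the active arm gains nothing further. The document gives no value for f or for the gain. The difference becomes 0.6(1 − f), and power = Φ(difference / √((φa + φb)/n) − 1.96).

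| f (assumed) | Difference | Power, 47 per arm | Power, 56 per arm |
|---|---|---|---|
| 0 | 0.60 | 80.6% | 86.9% |
| 0.10 | 0.54 | 71.9% | 79.2% |
| 0.25 | 0.45 | 56.3% | 63.7% |
| 0.50 | 0.30 | 29.2% | 33.8% |

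If those who cross over gain only half (0.3), a given f acts like half that f. For example, f = 0.20 gives 0.6 − 0.20 × 0.3 = 0.54, the 10% row. The 56-per-arm column keeps the 94% retention of the R code. At the 15% dropout for which those extra participants were added, power would be lower. The effect of unblinding on self-report is not modelled.

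**The case against.** The best contrary reading is that the open phase is a separate, optional extension. The wording makes joining a choice and an addition, whereas the three-month BPI is scheduled for everyone. The sentence stands among the benefits to participants, not in the design. The calendar gives the open phase its own row and its own analysis, and the printed dates do not overlap. Devices are returned at week 4 with a fixed session count, so early open use would need a deliberate re-issue, which the protocol nowhere describes. The mixed model also uses all time points, and the weekly BPI values up to week 4 are unaffected if open treatment began only after the device was returned.

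Much of this stands. The extension reading is plausible, and device return rules out casual continuation. It is not decisive, because the calendar gives project-level dates, its double-blind row is wrong on its face, and any open phase needs re-issue at a time nobody has fixed. The weekly data do not protect the contrast on which the trial is sized.

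A reader might go further and infer that sham participants did cross over, that the three-month result is invalid, or that the faulty dates prove overlap. The documents support none of these. No statement places open tDCS before moment 5, and the 10-day row on its own is a clerical error. Nor should the power table be read as giving a number of crossovers at which the trial fails, since that number moves with the assumed gain and dropout.

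**Conclusion.** The point holds as an unguarded endpoint, not as demonstrated contamination. Followed as written, the protocol lets sham participants receive known active tDCS before the self-reported BPI on which the trial is sized, and a reader cannot tell whether that could occur. The effect cannot be bounded from the document and may be zero. The illustrative powers rest on assumed uptake, full gain in those who cross over and no further gain in the active arm. The direction of bias depends on that last assumption. The sample size itself is correct and needs no change. The gap should be closed, because it bears on the sized comparison and costs almost nothing to close.

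**What to change.** State that open a-tDCS starts only after that participant's moment-5 BPI has been recorded. Correct the double-blind end date and say whether that row runs through moment 5.

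If anyone started open a-tDCS earlier:

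- report the number per arm from device session logs and re-issue records;
- run a sensitivity analysis that excludes BPI values after the first open session;
- present week 4 as the last fully blinded comparison.

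The cost is one sentence, one corrected table row and one count per arm. The Secondary Outcomes section describes the log download only at the end of treatment, so logs from any re-issued device would also be needed. One extra model run is required only if the count is not zero. No new participants are needed and the sample size stays at 112.

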## Study Discontinuation Criteria

The researchers had the prerogative to cease study participation if any clinical condition emerged that could endanger the patient's health or life. In the case of FIBRO-HB-tDCS, special attention was given to the emergence of suicidal ideation and/or planning, and (hypo)manic episodes, as depression is found in approximately 60% of fibromyalgia cases. In such situations, the participant was excluded from the study, regardless of when the issue arose, and referred for appropriate treatment.

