### **Inclusion Criteria**

Women aged 18 to 75 years; right-handed, literate, with a confirmed diagnosis of fibromyalgia (FM) according to the criteria of the American College of Rheumatology (2010-2016). These criteria required assessment using the widespread pain index (WPI) and the symptom severity score (SSS). Specifically, participants needed either a WPI score of at least seven, or a score between 4 and 6 accompanied by an SSS of 9 or higher or widespread pain in four out of five regions along with specific symptoms such as abdominal pain, depression, and headache within the last six months. In general, a combined WPI and SSS score of 13 or more was necessary as per the ACR-2016 standards. Moreover, participants were required to report a minimum score of 6 on the Numerical Pain Scale (NPS), which ranges from 0 to 10, for most days over the previous three months. They also had to agree not to change their doses of antidepressant and anticonvulsant medications during the study.

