Standard deviation of 1 unit

- Retention rates of 99%, 98%, 96%, and 94% at moments 2, 3, 4, and 5, respectively
- Autoregressive correlation matrix for MPII by BPI of 0.4 for the **a-tDCS** group

For the **s-tDCS** :

- Standard deviation of 1 unit
- Retention rates of 99%, 98%, 96%, and 94% at moments 2, 3, 4, and 5
- Autoregressive correlation parameter of 0.2.

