## Statistical Analysis

Continuous and categorical variables were compared using Fisher's exact test, the chi-square test, and the t-test for independent samples. The Shapiro-Wilk normality test was applied to determine the normal distribution of continuous variables. A Linear Mixed-Effects Regression Models for Repeated Measure (LMM) assessed primary outcomes (pain severity and disability) with treatment, placebo response (responder vs. non-responder), time, and the treatment-by-time interaction as fixed effects, and included a random intercept for patients to account for time differences. If appropriate, we then performed the Bonferroni's Test adjustment for post hoc multiple comparisons to identify differences between the groups at each time point and used a paired t test to assess the effects on each experimental group. The Generalized Linear Model (GLM) was used to examine the treatment effect on the secondary outcomes including quality of life, HPT, PGI-I and the descending pain inhibitory system (DPIS). The treatment effect on primary and secondary outcomes was adjusted for analgesic use and placebo susceptibility. Analgesic use was included in the model to control a potential confounder affecting pain outcomes. This ensures that the observed effects of a-tDCS and s-tDCS are attributable to the interventions rather than variations in analgesic use, thereby enhancing the validity of the results. All analyses were adjusted for multiple comparisons using Bonferroni's Test. The modified ITT (m-ITT) analysis included those completing  $\geq 50\%$  of sessions, with missing data imputed using regression model coefficients. In the m-ITT, with an adjusted protocol, encompassing all patients who completed at least ten sessions. The choice of ten sessions for ITT was guided by most of the literature supporting clinical symptom improvement in chronic pain. This method is not as strict as classical ITT, but it suggests that A-tDCS could be useful in clinical settings with at least a minimum number of sessions. Specifically, we replaced missing values with imputed data derived from a regression model using observed data. The treatment group served as the predictor, and the outcome variable with missing values was imputed based on regression coefficients, indicating the relationship between the treatment group and the outcome. This imputation method was applied, for example, to ten patients who withdrew after ten tDCS sessions. Sensitivity analyses confirmed consistent LMM results with or without imputation ([see per-protocol analysis in results - Supplement II](#)).

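### The discontinuation rule takes participants with a suicidal or (hypo)manic event out of the study at any time, instead of ending stimulation only, so their remaining BPI assessments are probably lost

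*Protocol*

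**What the plan says.** The Study Discontinuation Criteria first give the researchers discretion to end participation when a clinical condition endangers the patient. They then single out suicidal ideation or planning and (hypo)manic episodes, and state the consequence: "In such situations, the participant was excluded from the study, regardless of when the issue arose, and referred for appropriate treatment".

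Other sections that bear on this:

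- **Primary outcome and schedule.** BPI interference is assessed at baseline, at Weeks 1 to 4 and at the 3-month follow-up.
- **Sample size (f.4).** The 0.6-point contrast is set "at the final time point (moment 5), which occurs three months post-treatment".
- **Risks and Benefits.** "Participants could also join a 3-month follow-up phase, where a-tDCS -E-PEN was offered in an open phase".
- **Statistical Analysis.** The m-ITT keeps patients with at least ten sessions. On missing values: "The treatment group served as the predictor, and the outcome variable with missing values was imputed based on regression coefficients". On who received it: "This imputation method was applied, for example, to ten patients who withdrew after ten tDCS sessions". On the check: "Sensitivity analyses confirmed consistent LMM results with or without imputation".
- **Inclusion Criteria.** "They also had to agree not to change their doses of antidepressant and anticonvulsant medications during the study".

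**The concern.** Stopping a treatment and leaving a study are separate decisions. A suicidal or (hypo)manic event is good reason to stop stimulation and refer the participant. It is not in itself a reason to stop asking a willing participant for a BPI score. The rule makes both decisions at once, and at any time.

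The outcome most exposed is the 3-month BPI, which comes last and carries the sample size. The loss may also be related to treatment. The trigger is a change in mood, and the background (c.2) says that stimulation of the left DLPFC, the site used here, can relieve depressive symptoms. Such events could therefore differ in frequency between arms, and those affected could differ in pain interference from the rest of their arm. The protocol does not show whether either is so, or in which direction a bias would run.

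**Working it through.** **1. Reading the text.** The discontinuation section speaks of ceasing participation and of exclusion from the study. It does not mention stimulation. No other section describes assessments after such an exclusion. Loss of the later BPI is the natural inference, but it remains an inference.

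**2. The plan's own figure.** Inputs from f.4: difference 0.6, SD 1 in each arm, autoregressive correlation 0.4 (a-tDCS) and 0.2 (s-tDCS), retention 99%, 98%, 96% and 94% at moments 2 to 5, two-sided 5%, power 80%. The variance factors at moment 5 are 1.0597 and 1.0629.

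n per arm = (1.0597 + 1.0629) × (1.960 + 0.842)² / 0.6² = 46.28, so 47 per arm and 94 in all. With 15% dropout, 47 / 0.85 = 55.3, so 56 per arm and 112 in all. Both figures agree with the protocol.

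**3. Power.** With 56 per arm and 85% retention at moment 5, power is 83.8%. Assumed extra losses of 1, 2, 5 and 10 percentage points give 83.4%, 83.0%, 81.7% and 79.4%. Power is not the issue unless these events are frequent.

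**4. Possible bias (illustration, not a bound).** Let k participants with at least ten sessions be removed from one arm only, each with a true 3-month BPI d points from the mean of the rest of that arm, all in the same direction. Both k = 1 to 3 and d = 1 to 2 are assumptions. With the planning SD of 1, d = 2 means two standard deviations.

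*If the missing value is imputed from treatment group alone*, the participant receives the arm mean, and the error in the arm mean is k × d / 56:

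| k | d | Error | Share of 0.6 |
|---|---|---|---|
| 1 | 1 | 0.018 | 3% |
| 3 | 1 | 0.054 | 9% |
| 1 | 2 | 0.036 | 6% |
| 3 | 2 | 0.107 | 18% |

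*If the mixed model is fitted without imputation*, her earlier scores carry part of the deviation forward. Take a random intercept whose intraclass correlation equals the mean off-diagonal planning correlation:

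- a-tDCS: (4 × 0.4 + 3 × 0.16 + 2 × 0.064 + 0.0256) / 10 = 0.223
- s-tDCS: (4 × 0.2 + 3 × 0.04 + 2 × 0.008 + 0.0016) / 10 = 0.094

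A participant removed after treatment has five earlier scores: baseline and Weeks 1 to 4. If the deviation was already present at the four weekly scores, the share carried forward is 4 × ICC / (1 + 4 × ICC):

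- a-tDCS: 0.892 / 1.892 = 0.47
- s-tDCS: 0.376 / 1.376 = 0.27

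The remaining error is (1 − share) × k × d / 56. It runs from 0.009 to 0.057 points in a-tDCS (at most 9% of 0.6) and from 0.013 to 0.078 in s-tDCS (at most 13%). If the deviation arises only after removal, nothing is recovered and the table applies. If losses are balanced between arms or uninformative, the shift is 0.

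**5. Limits on k.** The protocol gives no count of these events. The 15% dropout allowance (0.15 × 56 = 8.4 per arm) and the ten withdrawals it mentions concern all causes, so they do not bound k usefully.

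**The case against.** The strongest reply is that this is a short clinical-safety paragraph that nowhere says data collection stops, and that nothing shows a single participant was affected. The Exclusion Criteria already screen out unstable psychiatric illness with a defined suicide risk, and the illustration needs several large deviations, all in one arm and in one direction. All of this stands. It limits the size of the point, but it does not change what the rule says.

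Several stronger readings are tempting, and the document does not support them:

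- *That the 3-month BPI is stated to be lost.* It is inferred from exclusion from the study.
- *That these exclusions were imputed from treatment group.* The imputation is described, by way of example, for patients who withdrew. Exclusions under this rule are not mentioned, and how they enter the analysis may be settled in an analysis plan that is not shown. That silence is not a fault of the protocol.
- *That exclusion after Week 4 serves no purpose because treatment is over.* It also keeps the participant from starting open-phase a-tDCS, which is a real safety function.
- *That most of the risk falls after treatment.* About 13 of 17 weeks (76%) lie there, but that is calendar time and not event risk. No assessment is scheduled between Week 4 and the 3-month visit.

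It can also be said that the analyses are reported as done, so an amendment comes late. That narrows what can still be changed, but it does not make the rule sound. Finally, a BPI score taken after new psychiatric treatment answers a somewhat different question. This is a genuine cost, and recording the treatment change makes it visible.

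**Conclusion.** The point holds as a cheap, minor improvement. As written, the rule can lose primary-outcome data for a reason tied to mood, although stopping stimulation and referring the participant would meet the safety need. That the BPI is lost rests on the plain reading of the rule.

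The effect on the result is probably small and cannot be quantified from the protocol. The figures of 0.02 to 0.11 points under group-only imputation, and up to about 0.06 (a-tDCS) or 0.08 (s-tDCS) in the non-imputed model, depend on assumed counts and deviations. They show scale only. A reader might take them as evidence that the primary result is biased, but the protocol gives no event rate, no split by arm and no direction, and the true shift may be 0.

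**What to change.** Amend the Study Discontinuation Criteria so that these events:

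- end stimulation;
- bar entry to, or continuation of, open-phase a-tDCS;
- trigger referral as now.

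The clinical criteria for stopping do not change. With consent, the participant stays in follow-up for whichever of the Week 4 and 3-month BPI assessments remain. In the m-ITT, use those observed values in place of imputed ones. Record any change of antidepressant or anticonvulsant dose, and report the events by arm for all randomised participants, including those stopped before the tenth session.

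The cost is a few amended sentences, a count by arm, and contact with a few participants who may decline. Some later BPI values may reflect new psychiatric treatment. The gain for the primary analysis is confined to participants with at least ten sessions, because the m-ITT leaves out the others. If follow-up is already complete, what remains possible is the report by arm, with a note of whether each case was observed, imputed or left out.
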